### Control group

The GPs in the control group attend a three-hour information evening session to learn about the case report forms and the patients’ inclusion/exclusion criteria. Their patients have the same schedule for visits as those in the intervention group (at 1, 4, 7, 10, 13, 19 months) but without specific education intervention.

### Statistical considerations

#### Sample size calculation and power analysis

The sample size required must accommodate the need to detect a difference between the intervention and control groups in the mean quality of life (sample size estimated for each domain of SF-36 and for the MLHFQ score) of 12 points with 90% power and 5% two-sided type 1 error taking into account clustering by practice (intra-cluster correlation considered to be between 0.10 and 0.20) [22], and an estimated 20% dropout rate for GPs and patients. As there is negligible information in the literature regarding SF-36 and MLHFQ assessment in intervention studies, a difference of 12 points was chosen using Brotons’ work [23] and the recommendations of Cohen [24] regarding variability of the quality of life indicators [16]. Estimation of the effect size (ES) can be achieved by a literature search, expert knowledge or using pilot studies. It is also possible to explore several scenarios using conventional effect sizes: small (ES = 0.2), medium (ES = 0.5) and high (ES = 0.8). Variability in the quality of life indicators is fixed for MLHFQ and SF-36 and corresponds to an effect size of ≥ 0.6 [17,24]. With these simulations, it is estimated that 40 general practices recruiting five patients each are required per group, therefore 200 patients per group. Overall, 400 patients from 80 GPs will be recruited.

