## Methods

### Study design and randomisation

The global study design is presented in Figure 1. ETIC is a cluster-randomised, controlled clinical trial with general practices as the unit of randomisation (Figure 2). The randomisation list was drawn up with the software Stata, version 10 (StataCorp, College Station, Texas, US) by the biostatistician before the start of the trial. A cluster design was chosen for pragmatic reasons and to avoid contamination bias. All GPs who volunteered were randomised and the patients did not know to which group their GP had been assigned. GPs that were located within the same practice represented a cluster and such GPs were placed in the same group to avoid cross-contamination. The trial is being carried out across the Auvergne in France, with stratification according to the 4 departments (administrative areas) in this region.

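### The stated inputs call for about 21 to 33 practices per group, not 40, so size and power do not match (in the conservative direction), and the target shifts from practices to GPs

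*Protocol article*

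**What the plan says.** All of the planning inputs stand in the protocol article under *Sample size calculation and power analysis*:

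- The target is a difference "of 12 points with 90% power and 5% two-sided type 1 error taking into account clustering by practice". It applies to each SF-36 domain and to the MLHFQ score.
- For clustering, the "intra-cluster correlation considered to be between 0.10 and 0.20".
- For losses, the plan allows "an estimated 20% dropout rate for GPs and patients". It does not say whether this is one combined 20% or 20% at each level.
- Variability is said to be fixed for both instruments at a value that "corresponds to an effect size of ≥ 0.6". No SD is printed.

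From unspecified simulations the section concludes that "it is estimated that 40 general practices recruiting five patients each are required per group, therefore 200 patients per group", and then: "Overall, 400 patients from 80 GPs will be recruited". The Abstract repeats the count of 80 GPs.

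Under *Study design and randomisation* the practice is the unit of randomisation, and "GPs that were located within the same practice represented a cluster". Under *GP recruitment and patient enrolment* the minimum of five patients applies to each GP, not to each practice.

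**The concern.** The section prints its inputs and its answer side by side, so a reader should be able to get from one to the other at least approximately. If that fails, the trial's stated sensitivity is unknown. Power of 90% for 12 points is the yardstick for a null result, and a trial that can in fact detect about 8 to 10 points supports a different reading.

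The change of unit is a second matter. Two groups of 40 practices make 80 clusters. Eighty GPs make 80 clusters only if no two of them share a practice, and the design section provides for shared practices.

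**Working it through.** **The plan's own figure.** The totals agree internally: 40 × 5 = 200 per group, 2 × 200 = 400 patients, 2 × 40 = 80 practices. What has to be reproduced is the 40.

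**Inputs.** Difference 12; effect size 0.6, the least favourable value that the plan allows, so SD = 12/0.6 = 20; z-values 1.96 and 1.2816 (sum 3.2415); five patients per practice; ICC 0.10 or 0.20; 1:1 allocation.

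**Step 1, individual randomisation.** n per group = 2 × 3.2415² / 0.6² = 58.4.

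**Step 2, design effect.** 1 + (5 − 1) × ICC = 1.4 at ICC 0.10 and 1.8 at ICC 0.20.

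**Step 3, dropout.** Divide by 0.8 for a single 20% loss, or by 0.8 × 0.8 = 0.64 if 20% of GPs and 20% of patients are both lost. Then divide by 5 and round up.

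| ICC | No loss | ÷ 0.8 | ÷ 0.64 |
|---|---|---|---|
| 0.10 | 81.7 patients, 17 practices | 102.2, 21 practices | 127.7, 26 practices |
| 0.20 | 105.1 patients, 22 practices | 131.3, 27 practices | 164.2, 33 practices |

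Rounding 58.4 up to 59 first turns the last cell into 59 × 1.8 / 0.64 = 166 patients, or 34 practices. No cell reaches 40.

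**Step 4, power of the stated design.** With one GP per practice, power = Φ(0.6 / √(2 × DE / n) − 1.96), where n is patients retained per group and DE = 1 + (m − 1) × ICC for m retained per practice.

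| Retained per group | ICC 0.10 | ICC 0.20 |
|---|---|---|
| 40 × 5 (no loss) | 99.9% | 99.4% |
| 40 × 4 (patients lost) | 99.7% | 98.9% |
| 32 × 5 (practices lost) | 99.5% | 97.9% |
| 32 × 4 (both) | 98.8% | 96.7% |

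A t-based check on the lowest cell gives 96.2%.

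**Step 5, difference detectable with 90% power at SD 20.** This is 3.2415 × √(2 × DE / n) × 20.

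- Best case after loss, 40 × 4 at ICC 0.10: 3.2415 × √(2 × 1.3 / 160) × 20 = 8.3 points.
- Worst case, 32 × 4 at ICC 0.20: 3.2415 × √(2 × 1.6 / 128) × 20 = 10.3 points.

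**Step 6, 80 GPs in fewer practices.** The number of GPs per practice is assumed, since the article does not give it. Each group has 40 GPs with five patients each. After 20% loss at both levels, 128 patients per group remain, in clusters of 4 × (GPs per practice). At effect size 0.6 and ICC 0.20:

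| GPs per practice | Retained cluster size | DE | Power |
|---|---|---|---|
| 1 | 4 | 1.6 | 96.7% |
| 1.25 | 5 | 1.8 | 94.7% |
| 1.5 | 6 | 2.0 | 92.4% |
| 2 | 8 | 2.4 | 87.3% |

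At ICC 0.10 power is still 95.7% with two GPs per practice. All rows treat clusters as equal in size; a mix of sizes would give slightly less.

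**The case against.** The strongest defence is that nothing here harms the trial. At the plan's own effect size the design exceeds 90% power, and more so because 0.6 is a lower bound. The planned baseline adjustment and repeated measures would usually add precision that this calculation ignores. The article refers to several scenarios, and a scenario table may sit in the full protocol. The Background says that most French GPs work alone, so 80 GPs may be close to 80 practices. All of this stands as regards direction and size. It does not explain how 40 came to be called required, because the printed inputs and the printed answer still disagree.

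Three stronger readings are tempting, and the document supports none of them.

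- **A power shortfall.** A reader might take the mismatch to mean that the trial is underpowered. At the stated inputs with one GP per practice the reverse is true. Sharing takes power below 90% only near two GPs in every practice, at the top ICC and with loss at both levels, which sits badly with mostly single-handed practice.
- **Low power for scores with a wide spread.** After the losses above, 90% power for 12 points holds up to an SD of about 23 to 29 (12/0.5125 and 12/0.413). At an assumed SD of 30 it would be 72% to 88%. The article gives no such SD and bounds it at 20, so this is a sensitivity range and not an error.
- **Effect size 0.5 as the true basis.** It gives 151.3/0.8 = 189.1 patients, or 38 practices, at ICC 0.20 with a single 20% loss. But an effect size of 0.55 with loss at both levels gives 40, and 0.5 with 20% lost at both levels has only 88.5% power. The article names 0.5 only as a conventional medium effect.

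**Conclusion.** The point holds as a mismatch between inputs, sample size and stated power, in the conservative direction. The plan's figures need about 21 to 26 practices per group at ICC 0.10 and 27 to 33 at ICC 0.20, against the 40 described as required. The excess is at least six practices per group even with the extra rounding. This rests on effect size 0.6, five patients per practice, the usual design-effect formula and 20% loss at one or both levels.

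The move from practices to GPs contradicts the article's own definition of a cluster. Its effect on power is modest unless shared practices are common, and the article does not say how common they are among participants. Neither point casts doubt on the adequacy of 400 patients at the stated effect size. Both affect how the result can be read, and correcting them is worthwhile because it is cheap.

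**What to change.** Rewrite the one paragraph, leaving enrolment as it is.

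1. Either state what the chosen size delivers, for example: *With 80 practices of five patients (40 per group), an SD of at most 20, an ICC of 0.10 to 0.20 and loss of 20% of practices and 20% of patients, power for a 12-point difference is 96.7% to 98.8%; the difference detectable with 90% power is 9.2 to 10.3 points.* (These are the 32 × 4 cases; 9.2 is 3.2415 × √(2 × 1.3 / 128) × 20.) Or, if 40 came from a smaller effect size, state that effect size and its SD as the planning basis. The sponsor must confirm which applies; a value of 0.5 should not be written in by inference.
2. Say whether the 20% dropout is one combined loss or applies at each level.
3. Give the target as 80 practices, and use a cluster size of five times the number of GPs wherever GPs share a practice.

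The cost is one rewritten paragraph.

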#### Statistical analysis

The statistician will be blinded with regard to treatment allocation. The responses to the questionnaire will be entered into a customised Access database (Microsoft, Redmond, Wash, US). Analyses will be made using Stata, version 13 (StataCorp, College Station, Tex, US). If necessary, an adjustment to accommodate differences between the baseline characteristics of the groups will be made. Continuous data will be presented as mean ± standard deviation (SD). The comparisons between study groups will be analysed using Chi-square or Fisher's exact test for categorical variables, and Student's or Mann–Whitney tests for quantitative variables, with normality verified by the Shapiro-Wilk test and homoscedasticity by the Fisher-Snedecor test. The correlation between SF-36 and MLHFQ will be assessed using Pearson’s correlation coefficient. Hierarchical linear regression models with random-effects levels for practice, individuals within practices and repeated measurements per individual (slope and intercept) will be used to estimate the effects of the intervention on SF-36 and MLHFQ scores for the post-baseline time points. These models will include an interaction factor between both the randomisation group and the particular time point, and will be adjusted for baseline SF-36 scores, age, gender, diagnosis, smoking history, treatment and socioeconomic status. Intra-class correlation coefficients will be presented by group. The secondary analyses will compare deaths (overall and due to heart failure) using Kaplan-Meier estimation and the Cox proportional-hazards regression model, hospitalisations (overall and due to heart failure), NYHA stage, treatment, adherence, weight and obesity between the groups with longitudinal random-effects models described previously. Estimation methods developed by Verbeke and Molenberghs will be used to account for missing data (GPs and patients) [25].

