### Instruments and outcomes

The primary outcome is the patients’ quality of life as measured by SF-36 [16] and the Minnesota Living with Heart Failure Questionnaire (MLHFQ) [17]. The SF-36 is a generic measure of health impairment, with scores ranging from 0 to 100: zero indicates the worst quality of life and 100 the best. The MLHFQ is specific for chronic heart failure and has 21 questions with scores ranging from 0 to 105: zero indicates best quality of life and 105 the worst. Quality of life is assessed at baseline and at 7, 13 and 19 months by the patients, or their main caregiver, within 7 days of their appointment with their GP. A score of < 24 on the MLHFQ signifies a good quality of life, a score between 24 and 45 signifies a moderate quality of life, and a score > 45 signifies a poor quality of life [18]. We will assess these cut-off scores to interpret results in clinical terms. We were unable to find published cut-off information for the SF-36 health scores.

The secondary outcomes are: all-cause and heart-failure-associated mortality; all-cause and heart-failure-associated hospitalization, number of days in hospital; the cumulative number of all cause death or HF hospitalizations and the cumulative number of days of hospitalisation; adherence with therapy; evolution of NYHA heart failure stage; evolution of treatment; and changes in weight and body mass index (BMI) at 19 months. We will assess guideline adherence of treatment at baseline and during the follow-up period. Patient adherence with therapy will be assessed by the patients themselves with a self-administrated questionnaire (validated in French) at baseline and at the end of follow-up period [19].

Should the planned follow-up appointment be missed, the reason is identified and categorised as follows: lost-to-follow-up; death; unable to attend for another reason. Hospitalisations and mortality will be recorded by GPs at each planned visiting case report form.

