### Intervention group

No medication is tested in this trial and the GPs are allowed to adapt patients’ treatment if necessary. The complex intervention consists of training at the GP practice with an interactive 2-day workshop to provide a patient’s education programme.

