For instance, one study on 240 patients with a mean age of 70 years and a majority of NYHA stage III (96.4%) reported baseline SF-36 mean scores of 45.1 in the intervention group and 46.8 in the control group [14]. The baseline MLHFQ mean scores were 42.5 and 42.6, respectively. In another study on 200 patients with a mean age of 63.5 years and a majority of patients with NYHA stage II-III (94%; 6% had stage IV), the baseline MLHFQ mean scores were 64.3 and 62.4 in the intervention and control groups, respectively [10]. In a study comparing home and hospital follow-up in 280 patients with a mean age of 71 years and slightly fewer patients with NYHA stage II-III (85%; 15% had stage IV), the baseline MLHFQ scores were 48.8 and 46.0, respectively [11]. In three other studies with 89%, 50% and 80% patients with NYHA stage III or IV, the mean MLHFQ scores were 49.3, 51.8, and 44.7, respectively [12,13,23]. Our patients will probably be older, with a better quality of life than the patients in all these studies because they are recruited in a primary care setting with NYHA stage I, II or III.

To our knowledge only one other cluster-randomised trial that measured the impact of a patient education programme by GPs has been published [23]. A total of 283 patients (mean = 76.3 years) were included: stage I – 1.8%; stage II – 7%; stage III – 38.9%; and stage IV – 50.5%. The mean MLHFQ score was 49.1 and 49.9 in the intervention and control groups, respectively.

The frequency of the visits in the ETIC trial, every 3 months, was similar to the standard of care; 87% of patients with heart failure meet their GP at least four times a year [38]. However, the educational aspects of the visits can be difficult for some of the GPs in the intervention group.

This study has limitations. The GP randomisation was done before the patient inclusions. The patients in the two groups might be different because the training received by the GPs in the intervention group may make them feel more competent and therefore, more inclined to include more severely ill patients. To avoid this bias, we could recruit randomised GPs after they had included their patients, using the ‘Zelen’ method [39]. Unfortunately, this has not been possible because the inclusion period lasts one year and the follow-up 19 months; regarding heart failure patient life expectancy, it would not be relevant [5].

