GPs participating in this study might be interested in patient education and not be representative of French GPs. This bias is inherent in any study because GPs must volunteer to participate. Otherwise, it would be possible that the usual care group could modify their medical practice, due to the observation, which is known as Hawthorne effect [40].

The power of this study might be too low to detect differences in mortality, hospitalisations and secondary outcomes. Our interpretation will not focus only on statistical significance but on the effect size and the magnitude of improvement describing the clinical relevance [41]. Therefore, the statistical analysis plan includes multivariate analyses with adjustment for differences in the characteristics between the two groups.

In France, some studies have assessed the impact of patient education for CHF patients [7,8]. However, these interventions were delivered from multidisciplinary teams, associated in part with the hospital. This trial will provide insight in the effectiveness of a complex intervention including a GP’s 2-day workshop and patient’s education programme in the setting of a GP consultation to improve the quality of life in patients with chronic heart failure in a pragmatic approach. This complex intervention could be a CHF management tool for use during initial and further medical training.

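### The covariate set of the primary analysis is left open to observed baseline differences, and the fixed list includes treatment without a time point

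*Protocol article*

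**What the plan says.** The Statistical analysis section of the protocol article contains two adjustment rules.

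- The first is conditional: "If necessary, an adjustment to accommodate differences between the baseline characteristics of the groups will be made". It is not attached to any particular outcome or model.
- The second is fixed. The hierarchical models for SF-36 and MLHFQ "will be adjusted for baseline SF-36 scores, age, gender, diagnosis, smoking history, treatment and socioeconomic status".

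The Discussion returns to the first rule and assigns it to the analysis plan: "the statistical analysis plan includes multivariate analyses with adjustment for differences in the characteristics between the two groups".

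Three other statements bear on this. Under Intervention group: "No medication is tested in this trial and the GPs are allowed to adapt" their patients' treatment. Under Instruments and outcomes, the secondary outcomes include "evolution of NYHA heart failure stage; evolution of treatment". In the Discussion, among the limitations: "The GP randomisation was done before the patient inclusions". The authors add there that trained GPs may tend to enrol sicker patients.

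**The concern.** A model's nominal error rate and interval assume that its covariates were chosen without looking at the trial data. The fixed list meets that condition and the conditional sentence does not. It makes observed imbalance, rather than prognostic value, the reason for adjusting, and it gives no rule for deciding when adjustment is needed. Nothing confines it to secondary or sensitivity analyses, so it can reach the primary quality-of-life models.

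The word treatment raises a separate problem. In the list, only SF-36 is marked as a baseline value. The models use repeated post-baseline measurements, so treatment could be entered as it stands at each visit. The workshop for intervention GPs covers treatment guidelines, so treatment during follow-up may be affected by allocation. Conditioning on it could remove or distort part of the effect being estimated.

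**Working it through.** **1. Design figures.** The article sizes the trial for "12 points with 90% power and 5% two-sided type 1 error", with "intra-cluster correlation considered to be between 0.10 and 0.20", an effect size of at least 0.6, and 40 practices of five patients per group. A 12-point difference at effect size 0.6 implies SD = 12/0.6 = 20, used below. The only stated figure is 200 patients per group. The standard formula gives 59 per group before clustering. With design effects 1 + 4 × 0.10 = 1.4 and 1 + 4 × 0.20 = 1.8, and division by 0.8 for dropout, that becomes 104 to 134. The stated 200 is not reproduced, but it lies on the safe side and does not bear on this point.

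**2. The two rules side by side.**

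| Element | Conditional rule | Fixed list |
|---|---|---|
| Variables | not named | seven named |
| Trigger | not stated | none needed |
| Scope | not stated | SF-36 and MLHFQ models |
| Time of measurement | baseline | stated for SF-36 only |

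The rules are compatible only if the conditional one is kept out of the primary models, and the article does not say so.

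**3. How often chance alone would trigger extra adjustment.** Assumptions, none from the article: K independent baseline variables beyond the fixed list, a trigger of p < 0.05, valid tests, and no true difference. Then P(at least one flag) = 1 − 0.95^K.

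- K = 5: 1 − 0.95^5 = 22.6%
- K = 10: 1 − 0.95^10 = 40.1%

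**4. What a triggered adjustment does.** I simulated 80 practices of five patients with no intervention effect, 3,000 runs per setting, analysed at practice level. Outcome coefficients per standardised covariate were 0.30 (K = 5) or 0.25 (K = 10); both are assumptions.

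| K | ICC | Triggered | Mean shift when triggered, points at SD 20 | Type I error: all covariates fixed in advance | Mechanical trigger | Most favourable of three models |
|---|---|---|---|---|---|---|
| 5 | 0.10 | 22.4% | 1.65 | 0.048 | 0.038 | 0.087 |
| 5 | 0.20 | 22.3% | 1.93 | 0.048 | 0.040 | 0.081 |
| 10 | 0.10 | 38.8% | 1.43 | 0.053 | 0.040 | 0.093 |
| 10 | 0.20 | 40.3% | 1.66 | 0.050 | 0.038 | 0.098 |

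The three models are unadjusted, triggered and fully adjusted. The shift is measured against the unadjusted estimate. It amounts to 1.43/12 = 12% to 1.93/12 = 16% of the target difference.

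**5. Treatment.** No arithmetic applies. Treatment can change after randomisation (Intervention group), is analysed as an outcome (Instruments and outcomes; Statistical analysis), and is a covariate without a date (Statistical analysis). Entered at its baseline value it is unobjectionable. Entered as current treatment it is a post-randomisation variable.

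**6. Severity.** The Discussion foresees an imbalance in severity, but the fixed list does not name NYHA stage. Stage is part of the inclusion criteria and its evolution is a secondary outcome, so the baseline value is collected. The imbalance the authors most expect is therefore one the conditional rule would probably be used to handle.

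**The case against.** The case on the other side has real weight.

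- **Scope.** The conditional sentence stands several sentences before the hierarchical models, among database, software and descriptive statements. The Discussion sentence follows a remark about low power for mortality, hospitalisation and secondary outcomes. A reader might infer that the primary estimate is certain to be data-driven; the text does not establish that. What stands is that nothing excludes it.
- **Error rate.** A reader might infer that the rule inflates the type I error. Applied mechanically in the simulation it did not: the rate was about 0.04. Inflation to 0.08 to 0.10 needs a deliberate choice of the most favourable result, and the article says the statistician is blinded to allocation. That limits selective choice. It does not make the covariate set independent of the data.
- **A larger false-flag figure.** The between-group tests named in the section ignore clustering. At design effects of 1.4 and 1.8, a nominal 5% test has true size 2[1 − Φ(1.96/√1.4)] = 0.098 to 2[1 − Φ(1.96/√1.8)] = 0.144. Over 10 variables that gives 1 − 0.902^10 = 64% to 1 − 0.856^10 = 79%. The arithmetic is right, but the article does not name these tests as the trigger, gives no count of variables, and states its ICC for the quality-of-life comparison only. Several likely variables are also already in the fixed list, so a flag on them would change nothing. I do not rely on this figure.
- **Treatment.** In a list of patient characteristics headed by a baseline score, baseline treatment is the natural reading. A reader might infer that the plan does adjust away part of the effect; the text does not show that. One qualifying word is missing.
- **Adjustment is needed here.** Because patients were recruited after practices were randomised, real imbalance is plausible and adjusting for prognostic factors is sensible. This stands in full. It is a reason to name those factors in advance, and it rules out a fix that simply restricts the model to the present list.

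**Conclusion.** The concern holds as a defect in a stated rule. The article sets an imbalance-driven adjustment of unspecified scope beside a fixed covariate list, so the covariates of the primary analysis can depend on the data. It also lists treatment without saying when it is measured.

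The size is modest and conditional. Under the assumptions in the working, chance alone would trigger extra adjustment in 23% to 40% of trials and move the estimate by about 1.4 to 1.9 points against a 12-point target. These figures assume no true baseline difference, whereas the article itself expects one in severity, so they illustrate the mechanism and do not predict what will happen in this trial. The treatment problem arises only if current treatment is entered. A fixed baseline covariate set is a better method at little cost, so the change should be made before analysis.

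**What to change.** 1. Delete the conditional sentence in Statistical analysis, or limit it to a sensitivity analysis labelled as such, and align the Discussion sentence with it.
2. State that the primary SF-36 and MLHFQ models use one covariate set, fixed now, whatever balance is observed, with every covariate as recorded at inclusion. Write baseline treatment in place of treatment.
3. Add baseline NYHA stage to that set, since severity is where the authors expect the groups to differ.

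The planned 400 patients are unaffected. The article reports the trial as ongoing, so the set can still be fixed before the data are analysed. The cost is a wording change and one more covariate. The sponsor also gives up the discretion to add covariates to the primary model after seeing the data. Adjusting for NYHA stage will not remove selection on unrecorded factors.

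### Unrestricted chi-square, Fisher, t and Mann-Whitney tests, and a Cox model for deaths with no practice term, sit beside otherwise sound practice-level models in a trial that randomises practices

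*Protocol article*

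**What the plan says.** The design is clear about the unit of allocation. Under Study design and randomisation: "ETIC is a cluster-randomised, controlled clinical trial with general practices as the unit of randomisation", and "GPs that were located within the same practice represented a cluster". The sample size section plans for this, with the "intra-cluster correlation considered to be between 0.10 and 0.20".

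The Statistical analysis section then gives three sets of methods:

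- **A general statement on group comparisons.** "The comparisons between study groups will be analysed using Chi-square" or Fisher's exact test for categorical variables, and Student or Mann-Whitney tests for quantitative ones. It adds checks of normality and equal variance for choosing among them. It names no cluster correction and no restriction to baseline.
- **Hierarchical models.** SF-36 and MLHFQ scores get random effects for practice, for patient within practice and for repeated measurements. Hospitalisations, NYHA stage, treatment, adherence, weight and obesity are referred back to the same kind of model.
- **Survival methods for deaths**, overall and from heart failure: "using Kaplan-Meier estimation and the Cox proportional-hazards regression model". No frailty term or cluster-robust variance is named.

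**The concern.** Patients of one practice share a doctor, a catchment area and, here, the intervention itself. A test that counts them as independent uses a standard error that is too small for a comparison between randomised practices. P values are then too low and confidence intervals too narrow.

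This affects three places:

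- **Deaths**, the first secondary outcome listed, whose stated method has no practice term.
- **Outcomes absent from the list of modelled outcomes.** The Instruments and outcomes section names a composite of all-cause death or heart-failure hospitalisation, days in hospital, and three MLHFQ categories for clinical interpretation. Days in hospital might be read as part of hospitalisations. The composite and the categories cannot, so the general statement is the only method that covers them.
- **Baseline comparisons.** The plan adjusts for baseline differences if necessary, and the Discussion concedes that recruiting after randomisation may make the groups differ. If unclustered tests decide which differences count, they will flag too many.

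For the modelled outcomes the section also leaves two methods standing and does not say which one governs inference.

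**Working it through.** **Inputs from the protocol.** 40 practices of 5 patients per group; ICC 0.10 to 0.20, set for quality of life; two-sided 5% error and 90% power; a 12-point difference that "corresponds to an effect size of ≥ 0.6"; 20% dropout for GPs and patients.

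**The plan's own figure.** Individual randomisation needs 2 × (1.96 + 1.2816)² / 0.6² = 58.4, so 59 per group. The design effect is DE = 1 + (m − 1) × ICC. With m = 5:

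| ICC | DE | 59 × DE | ÷ 0.8 (one 20% loss) | ÷ 0.64 (separate GP and patient losses) |
|---|---|---|---|---|
| 0.10 | 1.4 | 83 | 104 | 130 |
| 0.20 | 1.8 | 107 | 133 | 166 |

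The stated 200 per group is not reproduced exactly; the protocol refers to simulations and states no SD. It is larger than every variant tried, so the sample size is not in question here.

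**Error of a test that ignores practice.** The correct standard error is √DE times the naive one, so:

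true type I error = 2 × [1 − Φ(1.96 / √DE)]; coverage of a nominal 95% interval = 1 − that value.

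| Patients per practice | ICC | DE | √DE | 1.96/√DE | Type I error | Coverage |
|---|---|---|---|---|---|---|
| 5 | 0.10 | 1.40 | 1.183 | 1.657 | 9.8% | 90.2% |
| 5 | 0.20 | 1.80 | 1.342 | 1.461 | 14.4% | 85.6% |
| 4 (after 20% patient loss) | 0.10 | 1.30 | 1.140 | 1.719 | 8.6% | 91.4% |
| 4 (after 20% patient loss) | 0.20 | 1.60 | 1.265 | 1.550 | 12.1% | 87.9% |
| 5 | 0.01 (assumed) | 1.04 | 1.020 | 1.922 | 5.5% | 94.5% |
| 5 | 0.05 (assumed) | 1.20 | 1.095 | 1.789 | 7.4% | 92.6% |

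**Simulation check.** With 80 practices of 5, no true effect and 20,000 runs, the t test rejected in 9.7% (ICC 0.10) and 14.3% (ICC 0.20) of trials. The chi-square test, at an assumed 20% event rate, rejected in 10.0% and 14.8%.

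**Deaths.** The protocol gives neither an ICC nor an event rate, so both were assumed. An unclustered log-rank test (the Cox score test) was simulated with a shared gamma frailty per practice, 10,000 runs each:

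| Frailty variance (assumed) | 15% dead at 19 months | 25% dead at 19 months |
|---|---|---|
| 0 | 5.0% | 5.1% |
| 0.25 | 6.6% | 7.2% |
| 0.5 | 7.8% | 10.5% |
| 1.0 | 11.1% | 13.4% |

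**Larger clusters.** GPs who share a practice form one cluster, and each recruits at least five patients. If every cluster had 10 patients, DE would be 1 + 9 × 0.10 = 1.9 to 1 + 9 × 0.20 = 2.8, and the error 15.5% to 24.1%. The share of such practices is not given, so this is illustrative only.

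**The case against.** A reader might infer that the trial's between-group comparisons in general ignore clustering. The document does not support that. The hierarchical models are the ones said to estimate the intervention effect on SF-36 and MLHFQ. They carry a practice level, extend to most named secondary outcomes, and come with reported intra-class correlations. The sentence on simple tests follows remarks on baseline differences and on means with SDs, and precedes a correlation and the models. A descriptive or univariate step is therefore the natural reading. It stands as a likely intention, but the sentence sets no such limit, and some outcomes have no other stated method.

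A second objection is that the lack of a frailty term is only silence. A condensed article may leave it to the full analysis plan, and the sentence on secondary analyses could be parsed so that the random-effects models also cover deaths. The first half has weight: the article does not say that clustering will be ignored for deaths. The second is strained, because the models referred back to are linear models for repeated scores and do not suit time to death.

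Third, the ICC of 0.10 to 0.20 belongs to quality-of-life scores, which already have a practice effect. This stands in full. The 9.8% to 14.4% describes an unclustered test at that ICC, and neither the planned primary analysis nor the death analysis. The Discussion also warns of low power for mortality and says interpretation will rest on effect size as well as significance. That does not help with intervals, which would still be too narrow.

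**Conclusion.** The point holds in limited form, at moderate severity. The primary quality-of-life conclusion is protected by its model. What needs correcting is the unrestricted statement on simple tests and the Cox model with no stated allowance for practice. Both affect deaths, the unmodelled outcomes and any use of baseline tests to choose adjustments.

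For an outcome that clusters as strongly as the protocol assumes for quality of life, a nominal 5% test would have an error of 9.8% to 14.4% at 5 patients per practice. For deaths the size cannot be fixed from the document. At an assumed ICC of 0.01 to 0.05 it is a modest 5.5% to 7.4%; the larger simulated values depend on assumed frailty variances and mortality. The direction, standard errors too small whenever there is positive correlation within practice, does not depend on these assumptions.

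**What to change.** Amend the Statistical analysis section in three places:

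1. State that the chi-square, Fisher, Student and Mann-Whitney tests are descriptive only, or replace them for any inferential comparison with mixed or GEE models that take practice as the cluster. Name the model for the composite, days in hospital and the MLHFQ categories, and say that the hierarchical models govern inference wherever both methods could apply.
2. Fit the Cox models for all-cause and heart-failure death with a shared frailty for practice or a variance clustered on practice.
3. Present baseline characteristics descriptively, and do not use unclustered tests to decide on adjustment.

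The cost is a few sentences and standard software options, with no new data or patients. Intervals for the affected outcomes become slightly wider: by a factor of 1.02 to 1.10 at ICC 0.01 to 0.05, and 1.18 to 1.34 at 0.10 to 0.20, with 5 patients per practice.
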